## Abstract

**Background:**

Chronic cough is common and is associated with significant economic and human costs. While cough can be a problematic symptom without serious consequences, it could also reflect a serious underlying illness. Evidence shows that the management of chronic cough in children needs to be improved. Our study tests the hypothesis that the management of chronic cough in children with an evidence-based management pathway is feasible and reliable, and improves clinical outcomes.

**Methods/Design:**

We are conducting a multicentre randomised controlled trial based in respiratory clinics in 5 major Australian cities. Children (n = 250) fulfilling inclusion criteria (new patients with chronic cough) are randomised (allocation concealed) to the standardised clinical management pathway (specialist starts clinical pathway within 2 weeks) or usual care (existing care until review by specialist at 6 weeks). Cough diary, cough-specific quality of life (QOL) and generic QOL are collected at baseline and at 6, 10, 14, 26, and 52 weeks. Children are followed-up for 6 months after diagnosis and cough resolution (with at least monthly contact from study nurses). A random sample from each site will be independently examined to determine adherence to the pathway. Primary outcomes are group differences in QOL and proportion of children that are cough free at week 6.

**Discussion:**

The clinical management pathway is based on data from Cochrane Reviews combined with collective clinical experience (250 doctor years). This study will provide additional evidence on the optimal management of chronic cough in children.

**Trial registration:**

ACTRN12607000526471

## Background

Cough is the most common symptom presenting to primary care in Australia and internationally [1,2]. It is one of the most common reasons for referral to respiratory physicians. The burden of the symptom is considerable- both in terms of personal cost (e.g. impaired quality of life and multiple doctor consultations)[3] and at a societal level (through absences from school and work[4,5] and substantial medication expenses) [6]. Our previous studies have shown that >80% of parents of children with chronic cough have sought ≥5 medical consultations prior to referral [3]. Furthermore, ignoring cough (which may be the sole presenting symptom of an underlying respiratory illness) could lead to progression of a serious illness (such as bronchiectasis or retained foreign body in the airways) [7,8]. Paradoxically, cough is poorly researched. Patients are often inappropriately investigated and managed [9]. The need to improve the management of chronic cough in children is reflected in international[10-12] and Australian data [4,9], and our own collective experience.

The use of guidelines, recommendations, and clinical pathways can improve the quality of care [13,14]. Successful development of clinical guidelines requires many strategies. Initially, endorsement from experts and high quality of the evidence are important [15]. However, the use of guidelines is not universally popular in medical circles. "Numerous clinicians consider the compliance with tightened standards of care an impediment to their therapeutic freedom by imposing 'cookbook medicine' as a dogma" [14]. Also, provision of guidelines alone are not necessarily sufficient to change practice. However, the case for changing practice to be consistent with guidelines is much greater when the guidelines have been shown to improve patient outcomes. While multiple cough pathways exist, none has been subjected to a randomised controlled study [16]. Currently, the potential benefit of this type of management remains unclear. In our study, we will evaluate the feasibility and effectiveness of an evidenced-based clinical management pathway.

### Aims of the study

Our primary question in conducting the study is: Among Indigenous and non-Indigenous children with chronic cough, does management according to a standardised clinical management pathway (compared to usual treatment) improve clinical outcomes by 6 weeks? Our secondary aims are to:

1. Assess the reliability and validity of a standardised clinical management pathway for chronic cough in children; and

2. Compare the outcomes of chronic cough in Indigenous children with non-Indigenous children.

Our hypothesis is: The management of chronic cough in children in accordance with a evidence-based management pathway is feasible, reliable and improves clinical outcomes.

## Methods/Design

### Study design

We are conducting a pragmatic multi-centre randomised controlled trial (RCT) in urban respiratory specialist clinics in 5 major Australian centres: Brisbane, Melbourne, Sydney, Canberra and Darwin.

### Eligibility

Inclusion criteria: Children aged <18 years with chronic cough (>4 weeks duration)referred to a respiratory specialist for the first time. Exclusion criteria: Children with a known chronic respiratory illness previously diagnosed by a respiratory physician (eg cystic fibrosis).

### Recruitment

At each site, all referrals are screened by the site-specific study nurse. Parents are informed of the usual waiting times (6-8 weeks) and invited to participate. After informed consent, participants are randomised to either the active or control arms.

### Intervention and follow up

Children in the active arm enter the clinical pathway within 2 weeks of consent. They are managed according to the clinical pathway for at least 4 weeks before reassessment at 6 weeks (primary outcome). Children in the control arm enter the pathway at the usual waiting time (6 to 8 weeks). Since all of the participating clinics usually have a waiting time of at least 6 weeks, the control arm essentially represents usual practice. The enrolled child is managed according to the clinical pathway (figures 1 and 2). Each child is followed clinically until a primary diagnosis and cough resolution are achieved (max 12 months). Following cough resolution, children are followed-up (with monthly contacts) by the research nurse for a further 6 months. This follow-up is essential to document any recurrence of chronic cough and any additional respiratory diagnoses. To assess adherence to the pathway, a random sample of children's records (n = 10 to 20 per major participating centre: Brisbane, Sydney, Melbourne) will be examined.

**Figure 1 F1:**
[figure not shown]
**Pathway at entry point and non-specific cough**. Entry point of cough pathway and management for non-specific cough.

**Figure 2 F2:**
[figure not shown]
**Specific cough**. Pathway when specific cough pointers or abnormal CXR or spirometry (if aged >3-6 yrs) are present.

### Randomisation, allocation and blinding

The randomisation sequence was computer generated and used permutated blocks (4 or 6 participants per block). Children are randomised within two age strata (≤6years and >6years) and 5 site strata (Brisbane, Melbourne, Sydney, Canberra and Darwin). In Darwin, children are also be stratified by Aboriginality (as Aboriginal children in the Northern Territory are at an increased risk of chronic respiratory disease) [17]. The allocation sequence is concealed from all the investigators, participants and caregivers as done previously [18]. All primary outcome data are collected by telephone or by interview. The participants are informed (at each contact) that the person they speak to on the telephone should only be provided with direct answers to their questions. They are also advised that they can ring the clinical research staff directly if they need any additional information. The research nurse responsible for the primary outcome data collection received training on how to ensure the validity of clinical measurements. Through these means, we are confident that the person collecting the primary outcome data remain unaware of the allocation status of the participating child (outcome assessor blinded).

#### Data collection

All data are collected on standardized forms. Outcomes (PC-QOL and PedsQL) are collected at times weeks 0 (baseline), 6, 10, 14, 26, 52 and at study endpoint. Additionally, daily cough diary scores are collected till cough resolves. Demographic data (smoking, anthropometry, etc) and medical details are collected at baseline.

#### End point

Participation is complete when the primary diagnosis is established and cough resolved, in the presence of exit criteria, or at 12 months from time of enrolment (whatever is the earliest occurrence). Exit criteria are defined as child hospitalised for condition related to cough before primary diagnosis is made (eg. child has hypoxaemia related to interstitial lung disease), or child sought treatment elsewhere for cough. Children satisfying the exit criteria are considered 'clinical failures'.

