### Statistical analysis and reporting

Data will be reported and presented in accordance with the updated CONSORT criteria [30]. Children will be analysed according to allocation status (regardless of subsequent management). Clinical improvement will be defined by comparing: (a) the proportions of children who are cough free; and (b) the difference in PC-QOL at week 6 (with the intervention group being managed according to the pathway for at least 4 weeks). Efficacy of the clinical management pathway will be determined by improvements in both QOL measures and the percentage of children with a primary diagnosis achieved. Reliability will be determined by agreement in the implementation at each step of the pathway in children who have their medical records were re-examined. A kappa value of >0.6 will be considered acceptable for clinical practice (as recommended) [31]. Validity of the clinical pathway will be assessed by clinical failure rate (defined above), diagnosis reached by 12 months, and rates of misdiagnosis.

Unpaired and paired Student's T test will be used for continuous data comparisons (assuming normal distribution) and ANOVA utilised when >2 groups are compared. If data are not normally distributed, non parametric tests will be substituted. Chi squared tests will be used for categorical data. The 95% confidence intervals of all differences between the 2 study groups will be described.

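### Seeking treatment elsewhere counts as clinical failure from enrolment in both arms, so control children who use usual care during the 6 to 8 week wait are scored as failures before they reach the pathway

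*Protocol article*

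**What the plan says.** All references are to the protocol article; no separate analysis plan is shown.

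- **End point.** There are two exit criteria. One is hospitalisation for a cough-related condition before the primary diagnosis is made. The other reads "or child sought treatment elsewhere for cough. Children satisfying the exit criteria are considered" clinical failures. On follow-up the section states: "Participation is complete when the primary diagnosis is established and cough resolved, in the presence of exit criteria". The remaining limit is one year, counted from enrolment and not from pathway entry, and the first of these events to occur ends participation. Neither the arm nor the time since pathway entry limits the rule.
- **Abstract, Methods/Design.** Control is "usual care (existing care until review by specialist at 6 weeks").
- **Intervention and follow up.** "Children in the active arm enter the clinical pathway within 2 weeks of consent", whereas "Children in the control arm enter the pathway at the usual waiting time (6 to 8 weeks"). The section presents the control arm as essentially usual practice.
- **Outcome measures** lists the clinical failure rate as a secondary outcome.
- **Statistical analysis and reporting** states: "Validity of the clinical pathway will be assessed by clinical failure rate (defined above"), alongside diagnosis by 12 months and misdiagnosis. Children are analysed by allocation whatever their later management.

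**The concern.** Until a control child enters the pathway, the trial clinic gives no pathway care, so any cough treatment sought in that period comes from outside it. The document allows this as the control condition and also, read literally, scores it as failure. Exposure to the rule before pathway entry is unequal by design: 6 to 8 weeks in control against at most 2 weeks in the active arm, at least a threefold difference (6/2 = 3).

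Two uses of the failure rate are affected, in opposite directions. Between arms, extra failures fall on control and flatter the pathway. Taken over all children as a measure of the pathway's validity, failures in children not yet managed on it make the pathway look worse.

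A further consequence is possible. Because an exit criterion ends participation, a child who exits at, say, week 3 may have no week-6 value for cough freedom or PC-QOL, and such children would mostly be controls.

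**Working it through.** **1. Definitions side by side.** Take a control child who sees the family doctor for cough in week 3. Under the abstract's definition, the child is receiving existing care as allocated. Under End point, the child has sought treatment elsewhere, participation is complete, and the child is a clinical failure. Nothing in the article exempts this period. A control child who seeks no treatment while waiting is unaffected.

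**2. The plan's own figures.** No figure is given for clinical failure. The stated powers under Sample size do reproduce. For 35% against 55% with 110 per arm, two-sided 5%:
- SE under the null = √(2 × 0.45 × 0.55/110) = 0.0671
- SE under the alternative = √[(0.35 × 0.65 + 0.55 × 0.45)/110] = 0.0657
- With continuity correction: Φ[(0.20 − 1/110 − 1.96 × 0.0671)/0.0657] = 81.7%, matching the stated 82%. Without correction it is 85.1%.

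For PC-QOL (difference 1, SD 1.05, 25 per group), the noncentral t gives 91.0%, matching the stated 91%.

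**3. Illustration for the failure rate.** Assumed inputs: true failure 5% in both arms; a share f of controls seek care during the wait, independently of other failure; no active child does so before entry; 110 per arm; uncorrected two-sided 5% test. The apparent control failure rate is 0.05 + 0.95f.

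| f | Controls meeting the rule | Apparent failure, control vs active | Chance of a false result favouring the pathway |
|---|---|---|---|
| 10% | 11 | 14.5% vs 5% | 66% |
| 20% | 22 | 24.0% vs 5% | 98% |

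For f = 10%: null SE = √(2 × 0.0975 × 0.9025/110) = 0.0400; alternative SE = √[(0.145 × 0.855 + 0.05 × 0.95)/110] = 0.0395; Φ[(0.095 − 1.96 × 0.0400)/0.0395] = 66%.

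**4. What could happen to the week-6 cough outcome.** The article does not say how exits are handled, so these are alternatives and not predictions.
- *Exits lost at random.* Uncorrected power for 35% against 55% falls from 85% to 83%, 81% or 78% at f = 10%, 20% or 30%.
- *Exits scored as not cough free, care-seeking independent of resolution, no true effect.* The control rate becomes 0.35(1 − f) = 31.5%, 28% or 24.5%, and the test favours the pathway in about 8%, 20% or 40% of trials, against a nominal 2.5%.
- *Exits scored as not cough free, but all of them would still have been coughing.* The control rate stays at 35%, with no bias.
- *Exits excluded, all of them still coughing.* At f = 20% the control rate rises to 0.35/0.80 = about 44%, which works against the pathway.

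The sign changes with the handling rule and with who seeks care.

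**The case against.** **Meaning of elsewhere.** The control definition does not use the word. Treatment elsewhere could mean care outside the allocated management, such as another specialist; on that reading, a visit to the usual doctor is no exit. The sponsor may also have meant the rule to apply only after pathway entry. Either is possible, but the article says neither, and staff and analysts have only its wording to apply. This supports asking for reconciliation; it does not remove the conflict.

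**Use of the failure rate.** The analysis section ties it to pathway validity, both arms eventually enter the pathway, and the limitations section confines the randomised comparison to short-term outcomes. It may therefore be meant as a whole-cohort property. That is a fair reading, and the loading against control applies only if arms are compared. On the whole-cohort reading the rate is still contaminated, in the other direction.

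**Bias in the primary outcomes.** A reader might infer that the rule biases the week-6 results towards the pathway, with false-positive rates of 8% to 40%. The documents do not support this. Nowhere are clinical failures scored as not cough free, and analysis is by allocation regardless of management. Nor does completed participation plainly mean that data collection stops, since follow-up continues for 6 months after resolution. Handling of missing data may lie in a document not shown.

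**Frequency.** The Background reports ">80% of parents of children with chronic cough have sought ≥5 medical consultations prior to referral". That makes visits during the wait plausible but gives no rate for them. The 10%, 20% and 30% shares are assumptions.

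**Conclusion.** The point holds for the clinical failure rate and should be fixed. As written, one exit criterion overlaps with the control condition, applies from enrolment, and bears on the arms unequally before pathway entry. This is a stated rule that gives a wrong result, not a detail left to an analysis plan. A modest share of care-seeking would be enough to make a between-arm comparison uninterpretable (66% or 98% false findings at 10% or 20%, with 5% true failure, all assumed), and a whole-cohort rate would count failures that cannot be attributed to the pathway.

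For the primary outcomes, the supported conclusion is narrower: week-6 data may be lost, mainly in controls, with direction and size undetermined. A claim that the primary comparison favours the pathway would need a scoring rule that the article does not contain. Nor is all control-arm care scored as failure; only children who seek treatment during the wait are affected.

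**What to change.** 1. Reconcile End point with the abstract's control definition and with Intervention and follow up, stating from when, and in which arm, seeking treatment elsewhere is an exit criterion. That choice is the sponsor's.
2. For the analysis, count treatment elsewhere towards clinical failure only during time on the pathway, and report usual-care consultations before entry separately by arm.
3. State that children who meet an exit criterion keep their scheduled week-6 assessment and are analysed by allocation with observed values.

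**Cost.** Mostly wording, with slightly more follow-up effort, since the week-6 collection is already scheduled under Data collection. The reported control failure rate will be lower. An on-pathway rate describes the pathway and is not a clean randomised contrast, because controls whose cough resolves during the wait may never enter. Maximum time on the pathway also differs, since the 12 months run from enrolment: controls enter 4 to 8 weeks later (6 − 2 to 8 − 0). The report should say both.

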### Definitions used for clinical management pathway

• Asthma: Recurrent (>2) episodes of wheeze and/or dyspnoea that responds (within mins) to inhaled beta_2 _agonist, or bronchodilator resposiveness documented on spirometry (≥12% change in FEV_1 _%predicted after 400 ug salbutamol).

• Cough resolution: Improvement of ≥75% or total resolution according to cough diary data for ≥3 consecutive days [19,20]. When cough diary data are unavailable, resolution is defined as total cessation of verbal reporting of cough.

• CXR abnormality: Any abnormality (other than peribronchial thickening) as interpreted by specialist (respiratory or radiology).

• Primary diagnosis of aetiology of cough: Diagnosis confirmed by subsequent specific treatment which resulted in cough resolution within the expected time frame of <3weeks[20,21] (see above for time frame chosen). Diagnostic criteria are defined a-priori as published [22].

• Protracted bronchitis: (a) Presence of isolated chronic moist cough; (b) Resolution of cough with appropriate antibiotics; and (c) absence of an alternative cause for specific cough [20].

• Recurrent protracted bronchitis: ≥3 episodes per year of protracted bronchitis.

• Reversible airway obstruction: In accordance with American Thoracic Society and European Respiratory Society criteria with Australian predicted values used [23].

• Secondary diagnosis: Diagnosis found on objective tests but which: 1) specific treatment did not result in resolution or improvement of the cough; or 2) no treatment for this diagnosis was trialled and the cough resolved with other treatment or spontaneously [22].

• Specific cough pointers: Presence of any of the following- auscultatory abnormality, classical cough characteristics, cardiac abnormalities, chest pain, chest wall deformity, daily moist or productive cough for >3 months, digital clubbing, dyspnoea (exertional or at rest), failure to thrive, feeding difficulties (including choking/vomiting), haemoptysis, immune deficiency, neurodevelopmental abnormality, recurrent pneumonia, wheeze. These pointers are explained in TSANZ position statement [20].

• Spirometry abnormality: As determined by the American Thoracic Society and European Respiratory Society criteria with Australian predicted values used [23].

• Tertiary hospital management: Management that usually requires the level of investigations at a paediatric tertiary centre (bronchoscopy, chest HRCT scan, fluoroscopic swallowing screening, etc).

### Description of instruments for outcome measures

• Parent(s) proxy cough-specific QOL (PC-QOL): A validated multi-dimensional QOL designed for parents. This was modelled on Juniper's paediatric asthma QOL [24]. Each of the questions has a 7 point score, from one (worst) and 7 (best QOL). The scores to all the questions are added and the average is taken, thus one represents worst QOL and 7 represents best QOL [25,26].

• Cough diary: This validated scale is a verbal category descriptive score ranging from 0 (no cough) to 5 (cannot perform most usual activities due to severe coughing) [27].

• PedsQL™ 4.0[28]: This parent-proxy 23 item report for children is a generic validated multi-dimensional QOL designed for parental reports of their child's QOL. It is divided into 4 age groups (2-4, 5-7, 8-12, 13-18 years).

### Outcome measures

Primary outcomes for RCT: (a) proportion of children who are cough free; and (b) difference in PC-QOL at week 6 (with the intervention group being managed according to the pathway for at least 4 weeks). Secondary outcomes: change in PedsQL scores; proportion where a primary diagnosis was achieved; agreement of implementation of each step of the pathway (in the subset of children whose medical records were re-examined); clinical failure rate; diagnosis reached in number of children within the time frame of 12 months of enrolment; and proportion with recurrence of chronic cough related to original primary diagnosis (ie. possible misdiagnosis). As there are no published data on the outcomes of chronic cough in Indigenous children, the data from Indigenous children will be described separately.

### Sample size

To optimise the generalisability of the clinical management pathway, all children presenting to the clinicians over a 2 1/2 year period will be invited to participate. We anticipate enrolling approximately 220-250 children. This provides a sufficient power to address both primary outcomes. For a sample size of 220, the power to detect an improvement rate in the proportion of children whose cough has resolved[29] at week 6 from 35% to 55% using the pathway (compared to non-use of pathway) is 82% (significance 5%). For PC-QOL difference between groups of 1 (a clinically significant difference) assuming a SD of 1.05, a sample size of 50 (25 per group) yields a study power of 91%.

